## Abstract

**Purpose:**

The prevalence of severe vascular calcification in patients with Chronic Limb-Threatening Ischemia (CLTI) hinders the outcome of endovascular interventions and increases the risk of amputation and death. Intravascular lithotripsy (IVL) is a safe and effective treatment that promotes revascularization; however, large-scale data on its long-term effectiveness are lacking. The Chronic Limb-Threatening Ischemia treated with Intravascular Lithotripsy Observational Study (CALCIO) aims to address this shortcoming by assessing the real-world, long-term outcomes of IVL in a large cohort of patients with CLTI.

**Methods:**

CALCIO is a worldwide, multicenter, prospective cohort study designed to follow for 2 years 400 participants treated with the Shockwave Medical IVL System. Eligible patients, adults (≥ 18 years) with CLTI (Rutherford category ≥ 4) and calcified femoro-popliteal and/or crural lesions visible on fluoroscopy, are recruited upon providing informed consent. The primary outcome measure is a composite of wound healing and freedom from amputation at 12 months. Secondary outcome measures include technical success, amputation-free survival, changes in Rutherford category, limb perfusion and wound, ischemia, and foot infection (WIfI) score, patency, need for revascularization, safety, and patient-reported health-related quality of life (HRQoL). Results will be reported using mainly descriptive statistics. Patient enrollment opened in July 2024 and is planned to continue until July 2026, with the follow-up period expected to end in July 2028.

**Conclusion:**

CALCIO intends to provide valuable insights into the real-world long-term clinical outcomes of IVL to support decision making regarding the optimal endovascular treatment for CLTI patients. CALCIO is registered on ClinicalTrials.gov (NCT06149650).

**Graphical Abstract:**

[figure not shown]

## Introduction

Peripheral arterial disease (PAD) affects more than 100 million people worldwide and is associated with significant morbidity, mortality, and health-related quality of life (HRQoL) impairment [1, 2]. Endovascular interventions have become the primary revascularization strategy for PAD; however, the presence of vascular calcification reduces the effectiveness of many of these procedures by restricting vessel wall expansion, hindering drug absorption, and increasing the risk for procedural complications such as vascular dissection, stent fracture, and stent thrombosis [3–7]. In fact, severe calcification is a significant predictor of poor technical success and unfavorable clinical outcomes of endovascular treatments [8–11]. This is especially problematic for patients with Chronic Limb-Threatening Ischemia (CLTI), who show a high prevalence of severe, often circumferential femoro-popliteal and crural calcifications [11–13].

Intravascular lithotripsy (IVL) has been developed specifically to address these challenges using specialized balloon catheters that deliver sonic pressure waves to disrupt calcium deposits and thereby improve vessel compliance and revascularization outcomes. The technique’s safety and efficacy in achieving significant luminal gain have been demonstrated by two recent systematic reviews and meta-analyses, which reported an overall 55–60% reduction in diameter stenosis and low rates of periprocedural complications (~ 1.2%) [14, 15]. Despite these promising preliminary results, data on the long-term effectiveness of IVL remain scarce, particularly in CLTI patients.

The Chronic Limb-Threatening Ischemia treated with Intravascular Lithotripsy Observational Study (CALCIO) has been designed to address these important gaps in our understanding of the real-world performance of IVL for PAD by i) focusing specifically on patients with CLTI; ii) collecting 2-year follow-up data; iii) looking primarily at objective clinical outcomes that directly reflect patient quality of life (i.e., wound healing and freedom from amputation); and iv) supplementing these observations with patient-reported outcomes.

## Study Design and Site Selection

CALCIO is a prospective, multicenter, single-cohort, observational study. It is sponsored by the Cardiovascular and Interventional Radiological Society of Europe (CIRSE) and governed by a scientific Steering Committee composed of interventional radiologists with extensive expertise in the field of PAD. The study is conducted in compliance with the Declaration of Helsinki, good clinical practice, and all relevant European and national regulations and has received all necessary approvals from national or local ethics committees and regulatory authorities, if appropriate.

Sites in Europe and North America with expertise in the management of CLTI patients (≥ 50 CLTI patients treated per year) and experience with the Shockwave Medical IVL System (Shockwave Medical, Inc., California, USA; ≥ 10 cases to date) were invited to participate in the study. Approximately 40 sites across 9 countries (Austria, Canada, France, Germany, Hungary, Italy, Spain, Switzerland, the UK) are expected to contribute to the study.

## Study Population

A total of 400 patients with CLTI receiving IVL per standard of care will be recruited upon providing informed consent. Eligibility criteria are listed in Table 1. Principal investigators (PIs) are instructed to present the possibility to participate in CALCIO to all eligible patients and document refusal and reasons for non-eligibility when appropriate.

**Table 1 Tab1:** Patient inclusion and exclusion criteria

Inclusion criteria
1. Patient with Chronic Limb-Threatening Ischemia (Rutherford classification category ≥ 4)
2. Femoro-popliteal and/or crural calcified lesions visible on fluoroscopy
3. Treatment using the Shockwave Medical Intravascular Lithotripsy System

Exclusion criteria
1. < 18 years old
2. Incapacity or refusal to give informed consent
3. Ongoing pregnancy
4. Endovascular procedure(s) on the treatment site within 4 weeks before the planned intravascular lithotripsy treatment

Areas treated with IVL are referred to as “target segments,” and a segment is defined as a contiguous diseased area with less than 5 cm separation. Since there are no treatment restrictions, IVL may be performed on one or multiple segments, alone or with adjunctive endovascular interventions, on one or both limbs, on the same day or over multiple sessions. Patients may also receive endovascular or surgical procedures on non-target segments.

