## Data Collection and Quality Control

Baseline data, obtained within 6 weeks before the first planned IVL treatment, include demographics (age and sex) and relevant medical history (smoking habit, diabetes, hypertension, hyperlipidemia, symptomatic ischemic heart disease, ongoing anti-platelet/anti-coagulation treatment). Data specific to the target limb, including the presence and extent of ischemic ulcers and foot infection, measurement of limb perfusion (ankle–brachial index, ankle systolic pressure, toe pressure, or transcutaneous oximetry), and history of prior surgical or endovascular treatments for PAD, as well as data specific to the target segments, such as location, degree of stenosis, and length of occlusion (if relevant), are also captured. Upon completion of the first IVL treatment, procedural details, including information on any potential adjunctive intervention, are collected for each target segment together with digital subtraction angiography (DSA) images and non-contrast images taken from the unsubtracted mask of DSA images. In case patients do not receive IVL as planned, reasons for not proceeding with the planned treatment are recorded, and data collection is suspended (Fig. 1). For all treated patients, follow-up data are collected at 6, 12, and 24 months. Safety data are collected from the first IVL procedure throughout the study, and HRQoL is planned to be captured at each visit.

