#### Long-Term Effectiveness

To further assess the long-term effectiveness of IVL, **wound healing** and **freedom from amputation**, as defined above, will be reassessed at 24 months, and **amputation-free survival** will be reported from the time of the first IVL treatment, excluding patients with any amputation that had been planned beforehand.

Other secondary effectiveness outcome measures that will be assessed at 12 and 24 months include: i) changes of Rutherford category, limb perfusion, and WIfI score [16–18]; ii) **freedom from clinically driven target lesion revascularization (CD-TLR)**, defined as the absence of any endovascular re-intervention to the target segment (± 10 mm) or surgical bypass performed because of restenosis or occlusion and **CD-TLR-free survival**; and iii) patency of the target segments with a distinction between **primary patency** (absence of total occlusion without any re-intervention to the target segment); **assisted primary patency** (absence of total occlusion following re-intervention on the target segment due to restenosis); and **secondary patency** (absence of total occlusion following re-intervention on the target segment due to occlusion).

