#### Safety

Safety of IVL will be assessed by monitoring the incidence and severity of major adverse events (AEs) within 30 days after the procedure. These include, but are not limited to, procedural complications at the target and access sites (flow-limiting dissection, emboli, occlusion, infection, hematoma, false aneurysm, and perforation); deterioration of renal function; allergic reaction; sepsis; acute onset of limb ischemia; stroke and myocardial infarction. Severity will be graded according to the CIRSE classification system [19]. The total number of AEs and the percentage of patients with at least one AE will be summarized for AEs of i) any grade, ii) grade 3–4, and iii) grade 5. A further distinction will be made based on the likelihood of a causal relationship between the AE and the IVL procedure, as assessed by the PIs.

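### Staged IVL is allowed, but procedure data are tied to the first IVL treatment, and a planned second session on the same segment forfeits primary patency

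*Protocol article*

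**What the plan says.** Under Study Population, the article sets no treatment restrictions. IVL may be given to one or several segments, "on one or both limbs, on the same day or over multiple sessions". Any area treated with IVL is a target segment, and diseased stretches less than 5 cm apart belong to one segment.

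Under Data Collection and Quality Control, the trigger for procedural data is: "Upon completion of the first IVL treatment, procedural details, including information on any potential adjunctive intervention, are collected for each target segment". The DSA images and the non-contrast mask images are collected at the same point. The Immediate Effectiveness section then defines technical success of IVL and overall procedural success per treated segment, read centrally from DSA.

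Under Long-Term Effectiveness, primary patency is "absence of total occlusion without any re-intervention to the target segment". Assisted primary patency covers segments re-treated for restenosis, and secondary patency covers segments re-treated for occlusion. CD-TLR counts only procedures done because of restenosis or occlusion.

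Under Safety, the outcome is the "incidence and severity of major adverse events (AEs) within 30 days after the procedure". Table 2 gives the window as 30 days after IVL. Neither place says which session is meant. Collection itself is continuous: "Safety data are collected from the first IVL procedure throughout the study".

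**The concern.** The permitted treatment pattern is wider than the pattern that the data and outcome rules assume. Staged treatment is explicitly in scope, yet the request for procedural data and images names only the first treatment, and the patency rule does not separate a session planned from the outset from a re-treatment after failure.

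Two results are at stake. The per-segment success rates could rest on first-session segments alone, although they are presented as covering all treated segments. Images that were never requested cannot be recovered by an analysis rule. Primary patency could also be lowered by treatment that went exactly as intended.

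The article already sets planned events apart elsewhere. Amputations planned before the first IVL are reported separately in the primary outcome and lead to exclusion from amputation-free survival. Patency has no matching provision.

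**Working it through.** The plan states no figure that can be reproduced here. The target of 400 was set without a formal calculation, and no staging rate or expected patency is given. The check is mainly a comparison of rules, followed by an illustration.

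**Procedural data.** Take a segment first treated at a second session.
- It is a target segment, because it was treated with IVL.
- It belongs in the technical and procedural success outcomes, because these are defined per treated segment.
- Its details and images are not covered by the stated trigger, which is completion of the first IVL treatment.

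**Patency.** Take a segment that is open at 12 months and had a planned second session, with no restenosis or occlusion in between.

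| Category | Requirement | Met? |
|---|---|---|
| Primary | open, no re-intervention of any kind | no, if the second session counts as one |
| Assisted primary | open after re-intervention for restenosis | no |
| Secondary | open after re-intervention for occlusion | no |

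The segment is open but fits none of the three. This gap needs no assumed number. The 5 cm rule widens it, since a staged session on a neighbouring lesion can fall within the same segment.

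**Where the problem does not reach.** A later session on another segment or the other limb is not a re-intervention to the first segment. CD-TLR requires restenosis or occlusion. The primary outcome consists of wound healing and amputation and does not count repeat procedures.

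**Size for primary patency (illustration).** Let p be the primary patency that would be reported if planned sessions were not counted, and s the share of segments with a planned second session. If staging is unrelated to patency, reported patency is p(1 − s) and the loss is p × s. For scale, the 95% CI half-width is 1.96 × √(p(1 − p)/400), with one segment per patient. At p = 80% this is 1.96 × √(0.8 × 0.2/400) = 1.96 × 0.02 = 3.9 points. All values of p and s are assumptions.

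| p | Half-width (points) | Loss at s = 2% | 5% | 10% | 20% | s at which loss equals half-width |
|---|---|---|---|---|---|---|
| 70% | 4.5 | 1.4 | 3.5 | 7.0 | 14.0 | 6.4% |
| 80% | 3.9 | 1.6 | 4.0 | 8.0 | 16.0 | 4.9% |
| 90% | 2.9 | 1.8 | 4.5 | 9.0 | 18.0 | 3.3% |

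**Safety window.** If the 30 days were counted from the first IVL only, a session on day 15 would have 30 − 15 = 15 days of cover, and one on day 30 or later would have none. The text does not say that it is counted this way.

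**The case against.** The strongest reply is that a journal article condenses the full protocol. Repeat-form rules may stand there or in the eCRF, and the participant flowchart is not visible here. Procedural details are requested for each target segment, which could be read to include later ones. Re-intervention could also be read as treatment for lost patency, since the other two patency categories name restenosis and occlusion. Patency is one secondary outcome in a descriptive study with no confirmatory test. All of this lowers the weight of the point. It does not remove it, because the article itself states both the trigger and the patency definition. The trigger names the first treatment, and the definition excludes any re-intervention without an exception.

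A reader might infer more than the text supports:
- *That planned later sessions count as failures in general.* They do so only for primary patency and only on the same segment.
- *That complications of later sessions are missed.* Safety data run throughout the study, and the 30-day window is not tied to the first IVL. What is open is which session it refers to.
- *That staging 10 to 20% of segments costs 10 to 20 points of patency.* That would need true patency of 100%. The loss is p × s, so 8 to 16 points at 80%.
- *That clocks should start at the last planned session.* This would drop occlusions, re-interventions and amputations that occur between sessions.

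**Conclusion.** The point holds in a limited form. As worded, segments treated only at a later session have no procedural data or images for the technical and procedural success outcomes, and an open segment with a planned second session fails primary patency without fitting another category. Both follow from the text alone.

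The size is uncertain because the staging share is not given. At an assumed 80% patency, about 5% planned same-segment staging already costs as much as the 95% CI half-width at n = 400, and 10 to 20% would cost 8 to 16 points. At 2% the loss is 1.6 points, well inside the interval. These figures assume one segment per patient, all 400 patients evaluable, and staging unrelated to patency. With fewer evaluable segments the interval would be wider and the break-even share somewhat higher.

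The primary outcome and CD-TLR are not affected. The 30-day safety window needs clarifying, but the documents do not show that it understates complications.

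**What to change.** - State that the procedure form and the image upload are completed at every IVL session, so that each treated segment has data for central review.
- State that a session documented at the index procedure as planned is not a re-intervention for patency. Report such sessions separately, as is done for planned amputations.
- State that 30-day adverse events are reported after each IVL session. The data are already collected.
- Keep the first IVL as time zero for patient-level outcomes, and start each segment's clock at that segment's own first IVL, so that events between sessions are kept.

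The cost is extra entries on an existing form and clearer wording. The harder part is retrospective: 357 patients were already enrolled at submission, so staged cases among them need queries for images and planned status. Planned status should be taken only from records made at the index procedure, not judged later when the outcome may be known. Where no such record or image exists, report the segment as missing for that outcome.

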## Data Collection and Quality Control

Baseline data, obtained within 6 weeks before the first planned IVL treatment, include demographics (age and sex) and relevant medical history (smoking habit, diabetes, hypertension, hyperlipidemia, symptomatic ischemic heart disease, ongoing anti-platelet/anti-coagulation treatment). Data specific to the target limb, including the presence and extent of ischemic ulcers and foot infection, measurement of limb perfusion (ankle–brachial index, ankle systolic pressure, toe pressure, or transcutaneous oximetry), and history of prior surgical or endovascular treatments for PAD, as well as data specific to the target segments, such as location, degree of stenosis, and length of occlusion (if relevant), are also captured. Upon completion of the first IVL treatment, procedural details, including information on any potential adjunctive intervention, are collected for each target segment together with digital subtraction angiography (DSA) images and non-contrast images taken from the unsubtracted mask of DSA images. In case patients do not receive IVL as planned, reasons for not proceeding with the planned treatment are recorded, and data collection is suspended (Fig. 1). For all treated patients, follow-up data are collected at 6, 12, and 24 months. Safety data are collected from the first IVL procedure throughout the study, and HRQoL is planned to be captured at each visit.

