### Secondary Outcome Measures

#### Immediate Effectiveness

Immediate effectiveness, per treated segment, is defined as residual diameter stenosis ≤ 30% and will be assessed by BCIR using DSA images at the following time points: 1) after IVL and before any potential adjunctive intervention, “**technical success of IVL,**” and 2) by the end of the complete procedure after any potential, planned or unplanned, adjunctive intervention, “**overall procedural success.**”

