## Statistical Analysis

CALCIO is a single-arm study that will use mainly descriptive statistics to report the outcome measures. The target of 400 participants was not determined through a formal sample size calculation but was assessed by the Steering Committee as a sufficiently large sample to provide meaningful information on the treatment’s effectiveness while remaining achievable within the planned enrollment period. All participants who were planned to receive IVL will be included in the intent-to-treat (ITT) population, regardless of whether they received the planned procedure. In contrast, the modified intent-to-treat (mITT) population will only include participants who received IVL treatment.

The results of the primary outcome measure will be presented using summary statistics and a 95% confidence interval (CI). For time-to-event outcome measures (amputation-free survival) and (CD-TLR-free survival), median time-to-event and 95% CI will be calculated using the Kaplan–Meier estimator, while the impact of different covariates will be assessed using a stratified log-rank test and an univariable Cox proportional hazard regression. Following that, covariates with *p* values < 0.1 and ≤ 20% missing data will be included in a multivariable Cox proportional hazards regression model, while variables with p values < 0.05 will be retained in the model after backward elimination or if they contribute to the predictability of the model. All variables that were not included in the model due to extensive missing data will be listed. All other statistical tests will be based on a significance level of 5%, and estimates will be presented using 95% bilateral CIs. No adjustment for multiple testing will be done. In the analyses of time-to-event outcomes, data will be censored at the last time the patients’ status was assessed.

In general, no imputation of missing data is planned for the analyses, and missing observations will be presented as a percentage of the total. However, for the primary outcome measure, depending on the number of deceased and lost-to-follow-up participants before 12 months, a sensitivity analysis may be performed.

Given the absence of planned confirmatory hypothesis testing, findings should be considered exploratory. The statistical analysis will be conducted using the latest available versions of R and RStudio.

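### The ITT population includes patients in whom data collection stops when IVL is not given, so ITT adds nothing to mITT for follow-up outcomes, and technical success as worded appears to omit failed deliveries

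*Protocol article*

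**What the plan says.** The Statistical Analysis section defines two populations. For the first: "All participants who were planned to receive IVL will be included in the intent-to-treat (ITT) population, regardless of whether they received the planned procedure". For the second: "the modified intent-to-treat (mITT) population will only include participants who received IVL treatment". The same section says that imputation is, in general, not planned. It allows an optional sensitivity analysis of the primary outcome, depending on how many participants die or are lost before 12 months.

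The Data Collection and Quality Control section sets out what happens to the participants who separate the two populations: "In case patients do not receive IVL as planned, reasons for not proceeding with the planned treatment are recorded, and data collection is suspended". It continues: "For all treated patients, follow-up data are collected at 6, 12, and 24 months". Procedural details and angiographic images are gathered once the first IVL treatment is complete. Safety collection starts at the first IVL procedure.

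The Primary Outcome Measure section counts 12 months from the first IVL procedure, and the Long-Term Effectiveness section times amputation-free survival from the first IVL treatment.

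For technical success, the Immediate Effectiveness section states: "Immediate effectiveness, per treated segment, is defined as residual diameter stenosis" of at most 30%. The Study Population section reserves the term target segment for areas treated with IVL.

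**The concern.** There are two linked problems.

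First, an ITT population is useful for an outcome only if the outcome is observed, or handled by a stated rule, in the members who did not get the treatment. Here those members leave data collection at the point of non-delivery. A follow-up result labelled ITT would suggest protection against selection by successful delivery that the data cannot give.

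Second, a segment in which IVL is attempted but cannot be delivered is a failure of the technique. If only treated segments are scored, that failure is removed from the rate meant to describe how often the technique works. The Discussion expects the findings to feed into guideline and reimbursement discussions, where a reader may take technical success as the chance of success when IVL is tried. The same uncertainty touches safety: if a failed attempt does not count as an IVL procedure, its complications have no stated route into the 30-day summary.

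**Working it through.** The article gives no delivery-failure rate, technical-success rate or expected primary-outcome rate, and says of the sample size: "The target of 400 participants was not determined through a formal sample size calculation". There is no planned figure to reproduce. The check is a tracing of definitions, followed by illustrative arithmetic.

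**Step 1: can ITT differ from mITT on a follow-up outcome?**
- Members of ITT but not mITT are those planned for IVL who did not receive it (Statistical Analysis).
- Their data collection is suspended, and the 6-, 12- and 24-month visits are for treated patients (Data Collection and Quality Control).
- They have no first IVL procedure, so the primary outcome and amputation-free survival have no time origin for them.
- No imputation is generally planned, and the optional sensitivity analysis is tied to death and loss to follow-up, not to non-delivery.

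The participants with an observed outcome are therefore the same in both populations, and so is the estimate. Only the reported percentage missing would change.

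**Step 2: how much would an ITT primary result leave undetermined?** Assume 400 planned participants, a 60% primary rate among treated patients with otherwise complete data, and a non-delivery proportion d. Counting all undelivered patients as failures gives p(1−d); counting all as successes gives p(1−d)+d. The sampling half-width among the treated is 1.96 × √(p(1−p)/n).

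| d (assumed) | Undelivered | Treated | ITT bounds | 95% half-width, treated |
|---|---|---|---|---|
| 2% | 8 | 392 | 58.8% to 60.8% | 4.85 points |
| 5% | 20 | 380 | 57.0% to 62.0% | 4.93 points |
| 10% | 40 | 360 | 54.0% to 64.0% | 5.06 points |

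The width of the bounds equals d. At d = 10% the full width is 10.0 points, about the full width of the confidence interval (2 × 5.06 = 10.12).

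**Step 3: the technical-success denominator.** Three statements combine: target segments are areas treated with IVL (Study Population), images are collected on completion of the first IVL treatment (Data Collection and Quality Control), and success is scored per treated segment (Immediate Effectiveness). Read together, an attempted but undelivered segment is in neither numerator nor denominator. This could also happen within a patient who stays in mITT, because one patient may have several segments.

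Let s be success per treated segment and f the share of attempted segments not delivered. Success per attempted segment is s(1−f), and the overstatement is s − s(1−f) = s × f. With s = 90% (assumed):

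| f (assumed) | Per attempted segment | Overstatement |
|---|---|---|
| 3% | 0.90 × 0.97 = 87.3% | 2.7 points |
| 5% | 0.90 × 0.95 = 85.5% | 4.5 points |
| 10% | 0.90 × 0.90 = 81.0% | 9.0 points |

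Since s × f cannot be negative, the direction is fixed. This applies to technical success of IVL. Overall procedural success, scored after any adjunctive intervention, need not move the same way.

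**The case against.** The strongest reply is that the article defines two populations without assigning any outcome to ITT. Fig. 1, which is not shown, is captioned as linking the participant pathway to the data analysis and may assign follow-up outcomes to mITT. An ITT/mITT split with outcomes in mITT is ordinary in a single-arm cohort. This stands in part: the assignment may already be made. But neither the figure nor an analysis plan can supply outcomes that are not collected.

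A reader might infer that any result labelled ITT would be false. That goes too far. Baseline data precede the planned treatment and reasons for non-delivery are recorded, so baseline characteristics, proportion treated and reasons are valid ITT results. Nor is imputation ruled out absolutely; the text says only that none is planned in general.

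A reader might also infer that inclusion criterion 3, "Treatment using the Shockwave Medical Intravascular Lithotripsy System", contradicts ITT membership. Exclusion criterion 4 in the same table refers to the planned IVL treatment, and other sections use the same idea, so intended treatment is the natural meaning. At most this is editorial.

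On technical success and safety, no sentence says that failed attempts are excluded. The phrase about not proceeding can be read as covering cancelled or changed plans only. A patient in whom the device was introduced without effect might count as having had the first IVL procedure, so it cannot be said that complications of failed attempts go uncollected. This objection stands: the denominator problem is an inference from three definitions, and the safety problem is an ambiguity.

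Finally, success per treated segment is a legitimate, openly labelled quantity in a study that calls its findings exploratory. That limits the consequence but does not replace the per-attempt rate.

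**Conclusion.** The point about ITT holds on direct text: for any follow-up outcome, an ITT analysis of observed data would equal the mITT analysis.

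The point about technical success holds as a reading of the wording. Segments attempted but not delivered appear to leave the denominator, and that can only raise the rate. The size, 2.7 to 9.0 points, rests wholly on an assumed 90% success and 3% to 10% failed delivery. It would shrink if some failed attempts are already counted as treated. Whether complications of failed attempts are captured is undetermined.

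The study is descriptive, so the harm is a potentially misleading label and an optimistic technical-success rate, not an inflated type I error. The article does not support the conclusions that every ITT result is invalid, that failed-attempt complications are certainly lost, or that eligibility and ITT membership truly conflict.

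**What to change.** - State that follow-up outcomes are reported in mITT, and limit ITT to baseline data, the proportion treated and the reasons for non-delivery.
- Define when IVL counts as received, and split the recorded reasons into never attempted and attempted but not delivered.
- Report technical success per attempted segment, with undelivered segments counted as failures, alongside the rate per treated segment. Never-attempted segments stay out of both.
- Count attempted procedures as within safety collection where data exist, and say how many attempts lack 30-day data.

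The cost is analysis-plan wording, a small clarification of the case report form and a query to sites for the undelivered cases. With 357 of 400 patients enrolled at submission, most of that query is retrospective, and 30-day events may not be recoverable where collection was already suspended. Technical success will look slightly less favourable.
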